### Statistical analysis

Comparability between intervention and control groups will be assessed at baseline and at end of study to check for differences between participants, i.e. RNs and patients. Outcomes (KAS and BPI-SF) together with variables such as demographics, diagnosis, age, RN's length of experience and education, both at baseline and at end of study, will be compared between the intervention and control groups using both univariate and multivariate techniques [44]. Data will be analysed in accordance with the intention-to-treat principle. All participants with valid data regardless of whether they remained in the setting at baseline, drop-outs and losses to follow-up will be described.

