### Study design

This study will be carried out with a quasi-experimental design with non-equivalent control groups (Figure 1). Our rationale for a quasi-experimental design was that this type of design is known to be useful for testing causal hypotheses in field settings. It is acknowledged as a practical and feasible design while providing a systematic framework for answering questions relevant to 'real' clinical practice [23]. The design is also considered to be less intrusive on conditions in natural settings. It is important to acknowledge that due to the lack of randomisation, the intervention and control group may be systematically different. However, as it was not possible within the scope of this study to achieve a true experimental design a quasi-experimental design with non-equivalent control groups where the intervention can be separated from effects due to extraneous variables is preferred [23].

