### Setting, sample and sample size considerations

Participants (i.e. patients and RNs) will be recruited from two surgical wards specialising in patients with a cancer diagnosis at a hospital in South East Sweden. The hospital has 370 beds and provides services for approximately 150,000 people in the region. The intervention and control ward (26 beds on each ward) has 70 RNs and each year the wards admit around 820 patients who have been diagnosed with cancer.

Following negotiations on all organisational levels, both wards have agreed to participate in the study. The reason for this optimal numbers of participating RNs (n = 70) is that this study is seen within the organisation as providing support to the staff's annual education slots but also as part of supporting quality assurance of its care provision. Assignment to either the intervention ward or control ward is done by the research team.

Sample size calculations for the primary outcome measured by the Knowledge and Attitudes Survey Regarding Pain (KAS) are based on an expected 4.8 change in scores [24] among the RNs on the intervention ward and no changes among the RNs on the control ward. A significance level ᾳ of 0.05 (two-sided) and a power of 80% would require 33 RNs per group. Sample size calculations for the secondary outcome measure, the BPI-SF are based on the expectancy of a 1, 8 point decrease in total score regarding item current pain intensity among the patients on the intervention ward compared to the patients on the control ward [25]. Based on a significance level ᾳ of 0.05 (two sided) and a power of 95% this would require 30 patients per group.

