#### Outcome parameters

##### Primary outcome measure

Our primary outcome will be RNs' attitude and knowledge as measured using a modified version of the KAS [31] at baseline, four weeks and twelve weeks after the intervention for the RNs on the intervention ward (Figure 1). As there is a risk that the RNs on the control ward may be inadvertently exposed to the interventions, i.e. assessing their patients' pain intensity and pain impact on daily life, the RNs on the control ward will also be assessed at baseline and at twelve weeks to check for exposure biases.

The original KAS consists of 40 items where items 1-22 are false-true statements, items 23-36 are multiple-choice questions and items 37-40 consist of two case studies [31]. KAS has shown test-retest reliability (r > 0.80) [31] and internal consistency [32] range between 0.70 - 0.73 [31,33]. KAS takes around 10-15 minutes to complete and the number of correct answers is divided by the number of items (38) to produce the percentage of the total score [31]. We have removed two items as they were considered to be context-specific for the instrument's country of origin. The instrument has not been used in Sweden previously, hence a back translation by an authorised translator from English to Swedish was made.

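### The stated KAS analysis compares ward levels at each time point, not change, so a baseline gap between non-equivalent wards would pass into the end-of-study result

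*Protocol article*

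**What the plan says.** The Statistical analysis section of the protocol article is its only statement of the analysis. It says that the outcomes (KAS and BPI-SF), along with participants' education, experience, age, diagnosis and other demographics, "both at baseline and at end of study, will be compared between the intervention and control groups using both univariate and multivariate techniques". It also provides for a check of comparability between the groups at baseline and at end of study.

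Four other places bear on what the primary contrast should be:

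- **Study questions.** The first question asks whether the intervention improves RNs' knowledge and attitudes. That is a question about change.
- **Setting, sample and sample size considerations.** The calculation uses an "expected 4.8 change in scores [24] among the RNs on the intervention ward and no changes among the RNs on the control ward", which is a difference in change between wards. The same section notes: "Assignment to either the intervention ward or control ward is done by the research team".
- **Study design.** Without randomisation, "the intervention and control group may be systematically different".
- **Primary outcome measure.** The intervention ward completes the KAS at baseline, four weeks and twelve weeks. Of the control ward it says that "the RNs on the control ward will also be assessed at baseline and at twelve weeks to check for exposure biases".

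**The concern.** The study question and sample size are framed in terms of change, whereas the analysis sentence is framed in terms of levels at two times. In a randomised trial the two estimate the same effect on average. Here they do not. There is one ward per arm, the research team assigns the wards, and the article itself expects that they may differ. Any stable difference in KAS that exists before the workshops is still there at twelve weeks, and the end-of-study comparison counts it as effect. A gap in favour of the intervention ward can create a positive primary result, and a gap in favour of the control ward can hide a real one.

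The Primary outcome measure section adds ambiguity. It gives the control ward's KAS only one purpose, a check for inadvertent exposure, and does not call it the comparator for the primary outcome.

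The planned baseline comparability check offers little protection. A non-significant test with about 35 RNs per ward does not show that the wards are alike, and detecting a gap does not remove it.

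**Working it through.** **Inputs from the article.** Difference in change 4.8; a significance level "of 0.05 (two-sided) and a power of 80% would require 33 RNs per group"; 70 RNs on two wards, taken as 35 each (an even split is an assumption).

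**Inputs not in the article.** The SD of the KAS or of its change, the pre-post correlation r, and the true baseline gap. The gaps below are illustrative.

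**1. The article's own figure.** The 33 per group cannot be reproduced independently without an SD, but it can be inverted.

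- Normal approximation: SD = 4.8 × √(33/2) / (1.960 + 0.842) = 6.96.
- Two-sample t-test: 80% power at 33 per group needs d = 0.700, so SD = 4.8 / 0.700 = 6.85.

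So 33 is consistent with a two-group comparison if the SD is about 6.9. The article does not say whether that would be the SD of the score or of its change.

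**2. False positives when end-of-study levels are compared.** Let a gap of g SDs exist at baseline and persist, with no intervention effect. The end-of-study t-test at 33 per ward then has noncentrality g × √(33/2).

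| Gap g | Points at SD 6.85 | Share of 4.8 | Noncentrality | Rejection rate (nominal 5%) |
|---|---|---|---|---|
| 0.3 SD | 2.1 | 43% | 1.22 | 22% |
| 0.5 SD | 3.4 | 71% | 2.03 | 52% |

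The rejection rates depend only on g and n. The back-solved SD is needed only to turn g into points, and it serves that purpose only if it is the SD of the score.

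**3. The same in points, by normal approximation.** With SD 6.95, SE = 6.95 × √(2/33) = 1.71.

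| Gap (points) | Rejection with no effect | Power for a true 4.8 if the control ward is ahead by this much |
|---|---|---|
| 0 | 5% | 80% |
| 1 | 9% | 60% |
| 2 | 22% | 37% |
| 3 | 42% | 18% |

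**4. Does a baseline test catch the gap?** At 35 per ward and g = 0.5, the noncentrality is 0.5 × √(35/2) = 2.09 and power is 54%. The gap is therefore missed 46% of the time. The test reaches 80% power only at d = 0.679, or 0.679 × 6.85 = 4.7 points, close to the target effect itself.

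**5. What comparing change does.** If the intervention ward starts g ahead and stays g ahead, the difference in change is (effect + g) − g = effect. A stable gap cancels, whatever the SD or r.

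**6. Precision.** If 6.85 is the SD of the score, the SD of change is 6.85 × √(2(1 − r)), and the detectable difference at 33 per ward scales in the same way:

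- r = 0.3: 4.8 × 1.183 = 5.7
- r = 0.5: 4.8 × 1.000 = 4.8
- r = 0.7: 4.8 × 0.775 = 3.7

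If 6.85 is already the SD of change, the detectable difference stays at 4.8 for every r. The direction of any precision effect is therefore not known.

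**The case against.** The strongest reply is that the article leaves change unnamed but does not exclude it. Multivariate techniques could include a repeated-measures or baseline-adjusted model, the statistical reference is not at hand, and an article commonly leaves model form to a fuller plan. Read with the study question and the sample size, the analysis sentence can be taken as a loosely worded comparison of change. This stands in part: the text does not rule change out. It does not answer the sentence as written, which sets out between-ward comparisons at two times and lists participant characteristics, but not baseline KAS, as the accompanying variables. The choice of contrast is also more than model detail, because in this design it determines what is estimated.

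The gap sizes have no source in the article. That is correct, and the percentages show sensitivity, not a forecast.

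A reader might draw two stronger conclusions that the article does not support:

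- **That the primary analysis is a before-after comparison on the intervention ward alone.** The Primary outcome measure section gives a reason for measuring the control RNs. It does not set a single-ward analysis, and the Statistical analysis section compares KAS between groups.
- **That comparing change would sharpen the estimate.** This requires the back-solved SD to be that of the score and r to exceed 0.5. The test-retest reliability cited for the KAS is not a pre-post correlation across an intervention and twelve weeks in a modified, newly translated version. Below r = 0.5, change scores would be less precise than levels.

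**Conclusion.** The point holds as a mismatch between the stated analysis and both the question and the sample size, on the primary outcome of a design whose groups are admitted to be non-equivalent. Under the stated comparison, a persistent gap well below the 4.8 target can create or hide the result: about 22% and 52% false positives for gaps of 0.3 and 0.5 SD at 33 per ward, with a baseline test at 35 per ward missing the larger gap 46% of the time.

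The size depends on the actual gap, which is unknown, and on its being stable over twelve weeks. The conversion to points also rests on an SD of about 6.9 that the article does not state. The case is one of bias, and no gain in precision is claimed. Comparing change removes a stable gap, but with one ward per arm it cannot remove time trends specific to a ward.

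**What to change.** - **Statistical analysis:** name the between-ward difference in KAS change from baseline to 12 weeks as the primary contrast. Add as sensitivity an ANCOVA of the 12-week score on baseline KAS, length of experience and education. ANCOVA alone can leave part of a baseline gap in place in non-randomised groups, so it should support the change analysis and not replace it.
- **Baseline tests:** describe baseline differences, but do not let adjustment depend on their significance.
- **Primary outcome measure:** state that the control ward's KAS at baseline and twelve weeks is the comparator for the primary outcome, as well as a check for exposure.
- **Four-week KAS:** report it descriptively within the intervention ward. The control ward has no four-week measurement, so no between-ward contrast exists at that time.
- **Linkage:** keep a coded ID so that each RN's questionnaires can be joined across time points. The Ethical issues section says that data will be anonymised, so this needs to be reconciled with that statement.
- **Limitation:** state that with one ward per arm, ward-specific time trends cannot be separated from the intervention effect.

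The cost is wording plus the linkage code. The baseline and 12-week KAS on both wards are already planned, so no further measurement is needed.

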### Ethical issues

We will conduct the study in compliance with the established ethical guidelines of the Declaration of Helsinki [45]. Under the Swedish Ethical Review Act (2003:460) [46] this study does not need ethical clearance by a Regional Ethical Review Board, although we have nevertheless sought and received ethical guidance and advisory opinions from the Ethical Advisory Board in South-East Sweden (ref. 61-2011). All participants will receive verbal and written information about the study and will be informed of their right to withdraw at any time. To ensure compliance with the Data Protection Act [47], data will be stored securely and anonymised and only the research team will have access to the data. No published material will contain patient-identifiable information.

#### Obtaining informed consent from participants

Patients who meet the inclusion criteria on both participating surgical wards will be invited to take part in the study by the admitting RN or by the RN in charge of the patient. Both written and verbal information about the study and its protocol will be provided. All RNs on both wards will be informed verbally and in writing about the study before participating.

#### Risk and anticipated benefits for participants

This project will train RNs in the field of cancer-related pain and establish routines for pain assessment, which is good. Allowing the nurses to update their knowledge in cancer-related pain management may prove beneficial to other groups of patients experiencing pain. The findings of this study will be used to update present guidelines concerning cancer-related pain management. At present, no known risk can be envisaged concerning the patients' physical and/or mental health.

#### Forecast completion date

This study is due to be completed end of December 2011.

## Discussion

Nursing care is nowadays acknowledged as an increasingly complicated activity and "nursing complexity is such that it can be seen as the quintessential 'complex intervention" [48]. To be able to change and improve clinical practice thus demands multiple points of attack to meet complex challenges. Consequently, this paper presents a quasi-experimental study design that aims to i) endorse and assist behavioural change among nurses with regard to cancer-related pain and pain management and ii) change routine practice by implementing daily pain assessments. We expect the theory-based intervention to improve patient care as well as the quality of life for this group of patients but we also envisage that evidence-based guidelines targeting this patient group and their pain will be implemented more widely.

## List of abbreviations used

EPIC: European Pain in Cancer; KAS: Knowledge and Attitudes Survey Regarding Pain; RCT: Randomised Controlled Trial; RN: Registered Nurse; TPB: Theory of Planned Behaviour; VAS: Visual Analogue Scale.
